### Early termination of the trial

The Sponsor reserves the right to terminate the trial under the following conditions:
Safety concerns.Proven lack of efficacy.

If the trial is prematurely terminated or suspended, the investigator should promptly inform the subjects and ensure appropriate therapy and follow-up. Furthermore, the investigator and/or sponsor should promptly inform the pertinent ethics committee and regulatory authorities.

### Adverse events reporting

Information about Adverse Events (AEs), whether reported by the subject, discovered by the investigator by reviewing diary records, detected through physical examination, laboratory test or other means, must be collected and recorded on the AE form and followed up as appropriate.

Evaluation of AEs including severity, causality, outcome and seriousness assessments must be performed by a physician. Any AE occurring from the time the informed consent was signed by the subject and until 7 days after the last treatment day must be recorded and reported on an AE page in the eCRF*.* Standardised report forms for AEs and SAEs is provided as part of the eCRF.

### Definition of endpoints

#### Primary objective

To determine if empagliflozin can be used as a safe alternative to NPH insulin in patients with GIDM, with a tolerated significant difference in mean daily glucose (mean of CGM measurements) of up to 2 mmol/L to the higher side. Outcome measure: Mean glucose difference between the empagliflozin and NPH insulin group (calculated mean of CGM glucose profiles over the 2 first weeks of treatment). Calibration capillary glucoses values will be recorded. 70% of possible data (10 out of 14 days or 2822 out of 4032 possible tests) should be available for the patient to be included in the statistical analysis [11].

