### Discontinuation of IPs

Reasons to discontinue:
Wrongful randomization.Patient decision.AE, SAE etc. that contradicts further IP such as diabetic ketoacidosis.Non-compliance as judged by the investigator.Pregnancy.Hypoglycaemia defined as plasma glucose < 4 mmol/L at two different times in 24 h with at least 1 h between.Severe hypoglycaemia (need for assistance from others to restore blood glucose).Individual risk assessment of volume depletion/hypotension in acute illness, as judged by the investigator.Normalization of blood glucose after GK treatment is terminated.

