### Withdrawal from study

If a patient discontinues the IP, the patient will be replaced by further recruitment to maintain the required total minimum of 50 evaluable patients. Discontinuation of IP due to normoglycaemia after treatment with glucocorticoids are stopped within the 30-day treatment period will not be withdrawals and the visits will continue as planned.

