### Statistical analysis plan

Before the randomization code will be added to the cleaned dataset, a thorough plan for statistical analysis will be elaborated and accepted by the statistician and investigators. Intention-to-treat (all randomized subjects) and per-protocol statistical analysis will be conducted by the investigators (responsible: [name]), in collaboration with a statistician. All data will be described including data-incompleteness as well as reasons for data-incompleteness. Data will be analyzed blinded by the daily coordinator of the study [name] in collaboration with the principal investigator [name]. Any changes to the statistical analysis plan will be described in any future publications.

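### The 70% CGM-data rule for the primary endpoint cannot coexist with an intention-to-treat analysis of everyone randomised, and it can bias the non-inferiority comparison

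*Protocol article*

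**What the plan says.** Four parts of the protocol article bear on this.

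- *Statistical analysis plan*: "Intention-to-treat (all randomized subjects) and per-protocol statistical analysis will be conducted".
- *Primary objective*: the outcome is mean CGM glucose over the first two weeks, and 70% of the possible data (10 of 14 days, or 2822 of 4032 readings) "should be available for the patient to be included in the statistical analysis". No analysis set is named.
- *Withdrawal from study*, repeated under *Study design*: "If a patient discontinues the IP, the patient will be replaced by further recruitment to maintain the required total minimum of 50 evaluable patients". One type of stop is exempt: if drug is stopped because glucose is normal after the glucocorticoid has ended, such stops "will not be withdrawals and the visits will continue as planned". Nothing equivalent is said for other reasons.
- *Discontinuation of IPs*: the reasons to stop include "Hypoglycaemia defined as plasma glucose < 4 mmol/L at two different times in 24 h with at least 1 h between", and also severe hypoglycaemia. *Rationale for treatments* names hypoglycaemia as the main safety concern for NPH and calls the risk on empagliflozin very low.

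*Primary analysis* then concludes non-inferiority from a t-test and a 95% confidence interval against 2 mmol/L, without saying which analysis set is meant.

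**The concern.** The article fixes both rules itself, so this is not detail left to a separate analysis plan. An analysis of everyone randomised and an analysis of those with at least 70% of sensor data are different analyses, and for the primary endpoint only one of them can be the intention-to-treat result.

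Sensor completeness is known only after randomisation, and treatment can affect it. A patient who stops drug, is handled as a withdrawal and misses later visits is likely to fail the 70% rule. If such stops are commoner in one arm and linked to glucose level, the remaining groups are no longer the groups that were randomised, and replacement recruits do not restore that. In a non-inferiority trial the direction to worry about is the one that makes the arms look alike. Losing low-glucose NPH patients would raise the NPH mean and do exactly that.

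**Working it through.** **1. The plan's own threshold.** Readings every 5 minutes (*Rationale for study design and endpoints*) give 288 per day. 14 × 288 = 4032, and 0.70 × 4032 = 2822.4, so 2822 reproduces. Ten full days are 2880 readings, or 71.4%. The arithmetic is sound; the problem is which patients the rule applies to.

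**2. How a drug stop could become an exclusion.** Under *Visit procedures* the first sensor is removed and a second attached at visit 3, day 7. If the first sensor yields only its seven planned days and the patient does not attend visit 3, the most available is 7 × 288 = 2016 readings, 50% of 4032, which fails the rule. A patient who stops drug but keeps both sensors still qualifies. Continued visits therefore decide the matter, and they are stated for one type of stop only.

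**3. How many could fall outside.** *Power* has 74 randomised and up to 16 leaving: 74 − 16 = 58, and 16/74 = 21.6% (the text prints 25%). The replacement rule works to 50 evaluable: 74 − 50 = 24, and 24/74 = 32.4%. These are outer figures. The 16 covers both arms, all reasons and 30 days, whereas the primary endpoint covers 14 days.

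**4. Illustration of bias.** Suppose a fraction *f* of the NPH arm is excluded, with mean glucose *D* below that of the retained NPH patients, and there is no selective loss on empagliflozin. The full NPH mean is the retained mean minus *fD*, so the difference (empagliflozin minus NPH) is understated by *b* = *fD*.

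Inputs from the documents: margin 2 mmol/L, SD 2.6, 29 per arm, two-sided 95% interval. *f* and *D* are assumptions.

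SE = 2.6 × √(2/29) = 0.683. At a true difference of 2, the chance of a false non-inferiority claim is Φ(*b*/SE − 1.96), a normal approximation; with *b* = 0 it is 2.5%.

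| *f* | *D* (mmol/L) | *b* (mmol/L) | False non-inferiority |
|---|---|---|---|
| 5% | 1 | 0.05 | 3.0% |
| 10% | 2 | 0.20 | 4.8% |
| 15% | 3 | 0.45 | 9.7% |
| 21.6% | 2 | 0.43 | 9.2% |
| 25% | 3 | 0.75 | 19.5% |

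**5. Dependence on the other arm.** If 10% of each arm is lost and the lost patients are 2 mmol/L lower in both, the shift is −0.20 + 0.20 = 0. If the 10% lost on empagliflozin are instead 2 mmol/L higher, the shift is −0.20 − 0.20 = −0.40.

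**The case against.** Three stronger readings are tempting, and the documents do not support them.

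- *Replacement itself breaks intention-to-treat.* It does not. Replacing a patient adds a recruit; nothing says that the replaced patient leaves the randomised set. The firm conflict is the 70% rule. Replacement matters because it suggests that people who stop drug are counted as not evaluable.
- *NPH patients with hypoglycaemia are dropped.* No such exclusion is written. The 70% rule concerns sensor data, not drug status, and nothing says that CGM ends when drug stops. A patient who stops on day 4 but keeps wearing sensors qualifies, and so does one with complete data through day 10.
- *The bias is known to favour empagliflozin.* Two readings below 4 mmol/L need not mean a low 14-day mean, because the protocol describes this condition as mainly postprandial hyperglycaemia, often with normal fasting values. Glucose may also rise after NPH is stopped. Other listed reasons, such as ketoacidosis and volume depletion, could cause losses on empagliflozin that add to the shift or offset it.

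It is also fair to say that the article plans both analysis sets, a detailed analysis plan before the randomisation code is added, and a description of incomplete data with reasons. How missing data are modelled can properly wait for that plan.

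What survives is the contradiction. Describing missing data does not say whether a patient with 60% of readings is in or out of the intention-to-treat analysis, and the two sections answer differently.

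**Conclusion.** The concern holds as a contradiction between *Primary objective* and *Statistical analysis plan*. As written, the primary result labelled intention-to-treat would be a completer analysis. Its consequence is a possible bias: loss of CGM data can depend on treatment, and the stopping rules together with the expected hypoglycaemia on NPH make a shift towards non-inferiority plausible. The sign and size are not established. The range of about 3% to 20% for false non-inferiority, against 2.5%, rests wholly on assumed one-arm loss of 5% to 25% with a deficit of 1 to 3 mmol/L. It shows what the rule could allow and is not a forecast.

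**What to change.** 1. Under *Study design* and *Withdrawal from study*, state that CGM wear to day 14 and all planned visits continue for every randomised patient after study drug is stopped for any reason, unless consent is withdrawn, and that replaced patients stay in the intention-to-treat set. This concerns data collection only and changes no treatment.
2. Under *Primary objective*, make the intention-to-treat primary analysis include all randomised patients with any CGM data, for example by a mixed model of daily mean glucose, with a sensitivity analysis for those with none. Use the 70% rule only for the per-protocol analysis or a sensitivity analysis.
3. Under *Primary analysis*, name the set that carries the non-inferiority conclusion and report the per-protocol result beside it. I would not add a co-primary set limited to days on assigned drug and before rescue insulin, since that would bring back selection that depends on the outcome.

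Cost: a short amendment and analysis-plan wording. The sensors and visits are already planned. Patients with few CGM days add little precision, and there is slightly more analysis work. The first item is the urgent one, because CGM data not collected cannot be recovered later; the wording of the analysis should be settled before the randomisation code is added to the dataset.

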#### Secondary objectives

To determine if empagliflozin is non-inferior (in the below outcome categories) compared with NPH insulin in treating GIDM for the following CGM based outcome measures:

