**Methods:**

EANITIATE is a Danish, open, prospective, multicenter, randomized (1:1), parallel group study in patients with new-onset diabetes following treatment with glucocorticoids (> 20 mg equivalent prednisolone dose/day) with blinded endpoint evaluation (PROBE design). Included patients are randomized to either a Sodium-Glucose-Cotransporter 2 (SGLT2) inhibitor or neutral protamin Hagedorn (NPH) insulin and followed for 30 days. Blinded continuous glucose monitoring (CGM) will provide data for the primary endpoint (mean daily blood glucose) and on glucose fluctuations in the two treatment arms. Secondary endpoints are patient related outcomes, hypoglycaemia, means and measures of variation for all values and for time specific glucose values. This is a non-inferiority study with the intent to demonstrate that treatment with empagliflozin is not inferior to treatment with NPH insulin when it comes to glycemic control and side effects.

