##### TIR metrics

Between group differences in Time spent In Range (TIR) 3.9–10 mmol/L.

Between group differences of time glucose is above range (TAR) 10–13.9 mmol/L and 13.9–22.2 mmol/L.

Between group differences of time glucose is below range (TBR) 3–3.9 mmol/L and < 3 mmol/L.

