#### Safety objectives

To evaluate the safety and tolerability of empagliflozin compared with NPH insulin in treating GIDM. Outcome measures: SAEs. Discontinuation of investigational product (IP) due to adverse events. Changes in clinical chemistry/hematology parameters including finger prick ketones. AEs of interest (urogenital infections, volume depletion, diabetic ketoacidosis (DKA), HHS, hypoglycemic events and other AEs needing any treatment. Number of contacts between patient and general practitioner due to diabetes-related problems, and any admissions to hospital.

Percentage in each group that needing rescue medication due to hyperglycaemia. Outcome measure: Interviews and SP. Dose of sliding scale needed.

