#### Data presentation

Numeric data will be shown as mean or medians with inter-quartile ranges (IQR) or ranges where relevant. Frequencies will be shown as numbers with percentages and 95% confidence intervals (CI) where relevant. All statistical tests will be 2-tailed and *p* < .05 considered statistically significant. Any missing data will be presented in the appendix of the main manuscript.

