#### Secondary analysis

Continuous variables analysis will be done using a T-test. For categorical outcomes a Chi-square test will be used.

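### Non-inferiority is the stated objective for every secondary CGM outcome, but none has a margin and the named tests are two-tailed tests of difference, which cannot establish it

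*Protocol article*

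**What the plan says.** - **Objective.** The Secondary objectives section begins: "To determine if empagliflozin is non-inferior (in the below outcome categories) compared with NPH insulin in treating GIDM". This governs the lists under TIR metrics, Glucose exposure metrics, Glycemic variability metrics and Other metrics: 3 + 5 + 5 + 2 = 15 lines, and more once split by glucose level or time of day. Each item names a contrast and no tolerated difference, for example "Between group differences in Time spent In Range (TIR) 3.9–10 mmol/L".
- **Method.** The Secondary analysis section reads: "Continuous variables analysis will be done using a T-test. For categorical outcomes a Chi-square test will be used". Data presentation adds "All statistical tests will be 2-tailed", with significance at p below .05.
- **Margin.** The only one is 2 mmol/L for mean daily CGM glucose (Aims, Primary objective, Power, Primary analysis). The rule that compares a 95% confidence statement with that margin appears under Primary analysis only.
- **Side effects.** The Methods paragraph of the abstract gives the intent to show that "treatment with empagliflozin is not inferior to treatment with NPH insulin when it comes to glycemic control and side effects". The body's Safety objectives section says only "To evaluate the safety and tolerability of empagliflozin compared with NPH insulin in treating GIDM", with no hypothesis and no margin.

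**The concern.** A non-inferiority conclusion needs two things: the largest deficit that would be accepted, and evidence that the true deficit is smaller. A test of no difference supplies neither. If significant, it shows that the arms differ, and the deficit may still be one that everybody would accept. If non-significant, it says nothing about how large a deficit remains compatible with the data.

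For the primary endpoint the article supplies both parts. For the secondary CGM outcomes it makes the same kind of claim and supplies neither. This is a conflict between an objective and a method that are both written down, not a detail left for later.

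At stake is what the trial may say about time in range, time below range, variability and hypoglycaemic events. In a trial of this size a non-significant secondary result is quite likely even when empagliflozin is moderately worse. A report that followed the objective literally could present such a result as non-inferiority.

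**Working it through.** **1. The plan's own sample size.** Inputs from the Power section: difference 2 mmol/L, SD 2.6 mmol/L, 90% power, 29 completers per arm (58 in total), about 37 randomised per arm.

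n per arm = 2 × (z_alpha + z_power)² × (SD/difference)²

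- One-sided 0.05: 2 × (1.645 + 1.282)² × (2.6/2)² = 29, so 58 in total. This reproduces the stated figure.
- Two-tailed 0.05, as the text says: 2 × (1.960 + 1.282)² × (2.6/2)² = 36, so 72 in total. That difference is a separate matter.

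No sample size or power is given for any secondary or safety outcome.

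**2. Chance of a non-significant result when empagliflozin is truly worse.** For a continuous outcome with true deficit d in SD units, the t statistic is noncentral with 2n − 2 degrees of freedom and noncentrality d/√(2/n). At n = 29, √(2/29) = 0.263 and the two-sided 5% critical value is 2.003. For d = 0.5 the noncentrality is 0.5/0.263 = 1.90, just below the critical value, so slightly more than half of trials miss significance.

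| True deficit | 25 per arm | 29 per arm | 37 per arm |
|---|---|---|---|
| 0.3 SD | 82% | 80% | 75% |
| 0.5 SD | 59% | 54% | 44% |
| 0.77 SD (2/2.6) | 24% | 18% | 10% |

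The 25-per-arm column takes an even split of the 50 evaluable patients named under Withdrawal from study. The 0.3 and 0.5 SD rows are assumed sizes. The 0.77 SD row is the document's own primary margin divided by its own planning SD.

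By comparison, a rule that sets the limit of a two-sided 95% interval against a margin wrongly passes a treatment lying exactly at that margin 2.5% of the time.

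**3. Precision available.** Half-width of the 95% interval at 29 per arm = 2.003 × 0.263 = 0.53 SD.

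**4. What secondary non-inferiority would need.** The document gives no secondary margins, so a range is assumed (one-sided 0.025, 90% power, true difference zero):

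n per arm = 2 × (1.960 + 1.282)² / m², with margin m in SD units

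| Assumed margin | n per arm |
|---|---|
| 0.2 SD | 526 |
| 0.3 SD | 234 |
| 0.5 SD | 85 |
| 0.77 SD | 36 |

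With 29 to 37 per arm, only a very wide margin could be met with adequate power.

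**5. Side effects (binary, assumed rates).** Exact enumeration of the uncorrected chi-square test gives a non-significant result for true rates of 10% versus 20% in 81% of trials at 29 per arm and 77% at 37.

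**The case against.** - **The article never says that p above 0.05 will be taken as non-inferiority.** This is right. A reader might infer it because no other secondary rule is given, but the one rule the article does state, under Primary analysis, works properly by setting a confidence statement against a margin. The misreading is a risk left open, not a stated plan.
- **A t-test does not exclude an interval-based conclusion.** Also right: Primary analysis pairs its t-test with a 95% confidence interval, and the Statistical analysis plan section promises a fuller plan before treatment codes are merged with the data. That plan could set secondary margins. But the article already asserts the objective and names the tests, and as they stand they do not fit. The 2 mmol/L margin cannot be carried over to percentages of time, AUCs, coefficients of variation or event counts. It is not extended even to daytime and nocturnal mean glucose, which share its unit.
- **Side effects are not a non-inferiority objective in the body.** This stands. The wording is one sentence of intent in the abstract, and Safety objectives says only that safety will be evaluated. It is an inconsistency between abstract and body.
- **A reader might infer that the claim of a safe substitute for insulin rests on non-significant adverse-event tests.** The document does not support this. The Primary objective ties that claim to the 2 mmol/L margin and hence to the interval rule.
- **No section calls 0.3 or 0.5 SD material.** True. At the primary's own tolerated size the chance of non-significance is 18% at 29 per arm, so non-significance is not the likely outcome for a deficit that large.
- **Much of the estimation wording is already there.** The listed items are phrased as group differences, and Data presentation allows 95% intervals for frequencies. This makes the repair small; it does not remove the conflict in the lead-in sentence.

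**Conclusion.** The point holds as a mismatch between objective and method. The secondary CGM outcomes carry a non-inferiority objective, none has a margin, and the named two-tailed difference tests cannot deliver that conclusion without one. As written, either nothing can be concluded or a non-significant result could be misread.

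The size of that risk at 29 completers per arm is 54% for a true deficit of 0.5 SD and 18% for one of 0.77 SD. These figures assume normally distributed outcomes, equal arms and equal variances, and the 0.5 SD deficit is an illustration. The abstract's extension of non-inferiority to side effects is a smaller, separate inconsistency.

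It should not be concluded that the trial plans to equate non-significance with non-inferiority, or that the primary endpoint's decision rule is affected. The change should be made because it alters what may be claimed, but it does not threaten the primary conclusion.

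**What to change.** 1. Replace the lead-in to Secondary objectives with: *To estimate between-group differences, with 95% CIs, in:*. Label these outcomes supportive, and state that p above 0.05 is not evidence of non-inferiority.
2. If the sponsor wants to keep a secondary non-inferiority claim (time in range, for example), fix its margin before the treatment codes are added to the data, compare the relevant 95% confidence limit with it, and test it only after the primary succeeds.
3. Drop side effects from the non-inferiority sentence in the abstract, so that it agrees with Safety objectives, and report side-effect rates by arm with exact 95% confidence intervals. This shows the reader what the trial can exclude: zero events among 37 randomised patients in an arm leaves a one-sided 95% upper bound of 1 − 0.05^(1/37) = 7.8%, or 1 − 0.025^(1/37) = 9.5% at one-sided 97.5%.

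The cost is wording only, with no change to data collection, sample size or the primary analysis. The trial gives up secondary non-inferiority claims that it could not support.

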##### TIR metrics

Between group differences in Time spent In Range (TIR) 3.9–10 mmol/L.

Between group differences of time glucose is above range (TAR) 10–13.9 mmol/L and 13.9–22.2 mmol/L.

Between group differences of time glucose is below range (TBR) 3–3.9 mmol/L and < 3 mmol/L.

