##### Glucose exposure metrics

Between group differences in AUC for blood glucose during periods when blood glucose levels reach 10–13.9 mmol/L and 13.9–22.2 mmol/L.

Between group differences in AUC for blood glucose during periods when blood glucose levels reach 3–3.9 mmol/L and < 3 mmol/L.

Between group differences in mean daytime blood glucose levels.

Between group differences in mean nocturnal blood glucose levels.

Between group differences in eHBA_1c_.

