##### Other metrics

Between group differences in number of hypoglycemic events in total and divided into levels (3–3.9 mmol/L, < 3 mmol/L or a need for third party assistance to restore blood glucose).

and nighttime/daytime.

Between group differences in number of hyperglycemic events in total and divided into levels and nighttime/daytime.

Hypo- and hyperglycemic events are defined as at least 15 min spent in the specific range and each event must be at least 30 min apart. Nighttime is defined as midnight – 6. am [11].

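### Time in the closed 10–13.9 mmol/L band has no single harmful direction, so a non-inferiority statement or t-test on that band alone can miss or reverse a real worsening

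*Protocol article*

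**What the plan says.** All references are to the protocol article.

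- TIR metrics lists three items. For values in the target zone it names one range: "Between group differences in Time spent In Range (TIR) 3.9–10 mmol/L". For high values it names two bands, each with an upper limit: "Between group differences of time glucose is above range (TAR) 10–13.9 mmol/L and 13.9–22.2 mmol/L". For low values it names one closed band and one that is open downwards: "Between group differences of time glucose is below range (TBR) 3–3.9 mmol/L and < 3 mmol/L". None of the three is total time above 10 or total time below 3.9 mmol/L.
- Secondary objectives states the purpose of these outcomes: "To determine if empagliflozin is non-inferior (in the below outcome categories) compared with NPH insulin in treating GIDM".
- Secondary analysis names the method: "Continuous variables analysis will be done using a T-test". Data presentation makes all tests two-sided at the 5% level.
- Other metrics does ask for a total where events are counted: "Between group differences in number of hypoglycemic events in total and divided into levels". The time outcomes have no such total.

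**The concern.** A non-inferiority statement needs an outcome for which one direction is harmful. Time in 10–13.9 mmol/L does not have one. A lower share may mean that readings moved into range, or that they moved into the band above. A non-inferiority margin does not cure this, because the margin must sit on a known harmful side. The 3–3.9 band has the same structure: time can leave it upwards into range or downwards below 3.

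At stake is the reading of individual secondary results. A row labelled time above range at 10–13.9 could show no difference, or a significant advantage, for the arm with higher glucose. Under the stated objective, that row could be written up as non-inferiority in its own right.

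**Working it through.** The article states no figure for the time bands, so there is none to reproduce. The check asks how the band behaves as mean glucose rises.

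**Inputs from the article**
- Band limits 3, 3.9, 10, 13.9 and 22.2 mmol/L (TIR metrics).
- 29 completing patients per arm, SD 2.6 mmol/L, and SD 4.2 mmol/L across 1131 single readings (Power).
- A gap of 2 mmol/L, the tolerated difference in mean glucose (Primary objective).
- Two-sided t-test at 0.05.

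**Assumptions not in the article**
- The arm means.
- Normal readings within a patient.
- Use of 2.6 as between-patient SD and 4.2 as total SD, so that within-patient SD = √(4.2² − 2.6²) = √10.88 = 3.30.

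**Step 1: shape of the band.** For a patient with mean m and within-patient SD s:
- share in 10–13.9 = Φ((13.9 − m)/s) − Φ((10 − m)/s)
- share above 10 = 1 − Φ((10 − m)/s)

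The first is largest at m = (10 + 13.9)/2 = 11.95. With s = 2.6 it is 43.3% at mean 10, 51.7% at 11, 54.7% at 12, 51.1% at 13, 42.3% at 14 and 30.9% at 15. Share above 10 rises throughout, from 50.0% at mean 10 to 97.3% at 15.

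**Step 2: simulated trials.** Patient means were drawn from N(arm mean, 2.6²), with s = 3.3, 29 per arm and 20,000 trials per row. The second arm is always 2 mmol/L worse. The last five columns give the percentage of trials with p < 0.05 in the stated direction.

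| Arm means | Time in 10–13.9 | 10–13.9 favours worse arm | 10–13.9 shows harm | >10 shows harm | 13.9–22.2 shows harm | TIR shows harm |
|---|---|---|---|---|---|---|
| 8 vs 10 | 23.7% vs 32.4% | 0 | 72 | 81 | 73 | 58 |
| 9 vs 11 | 28.5% vs 34.9% | 0 | 55 | 81 | 76 | 73 |
| 10 vs 12 | 32.3% vs 35.8% | 0.1 | 22 | 81 | 78 | 78 |
| 11 vs 13 | 34.9% vs 34.7% | 3 | 2 | 80 | 80 | 80 |
| 12 vs 14 | 35.7% vs 32.0% | 25–26 | 0.1 | 78–79 | 80 | 79 |

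Ranges are the spread over repeat runs.

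**Step 3: sensitivity at 12 vs 14.**
- Between-patient SD 1.5, within-patient SD 3.0: the band favours the worse arm in 90% of trials. The 13.9–22.2 band and TIR each show the harm in over 99%.
- Lognormal readings, single patient: the band share goes from 49.6% to 43.1% (CV 25%) and from 36.9% to 35.3% (CV 35%). The reversal does not depend on normality, but its size does.

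**Step 4: how often the listed set misleads as a whole.** At 12 vs 14 (SDs 2.6 and 3.3), the 10–13.9 band favours the worse arm while neither 13.9–22.2 nor TIR shows harm in about 1 to 1.5% of trials.

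**Step 5: the low band.** Under a shift in mean alone, time in 3–3.9 reverses only below a mean of (3 + 3.9)/2 = 3.45 mmol/L. At mean 8 it stops rising with spread once within-patient SD passes about 4.5: 4.76% at SD 4.2, 4.75% at 5 and 4.49% at 6, while time below 3 goes from 11.69% to 15.87% to 20.23%. In simulated trials at means of 8 to 14, average time in 3–3.9, below 3 and below 3.9 always moved together.

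**Step 6: the upper cap.** The 13.9–22.2 band omits time above 22.2. At mean 14 this is 0.1% of time with total SD 2.6 and 2.5% with total SD 4.2.

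**The case against.** The strongest reply is that nobody would read the 10–13.9 row alone. The same sentence lists 13.9–22.2, and the line before it lists time in range. In the rows where the band fails (10 vs 12, 11 vs 13, 12 vs 14), each of those detects the harm in about 78–80% of trials, against 78–81% for time above 10. Less time at 10–13.9 beside much more at 13.9–22.2 correctly describes an upward shift. The group mean of time above 10 can also be recovered as 100% minus TIR minus time below 3.9: 100 − 29.0 − 2.7 = 68.3% and 100 − 16.2 − 0.8 = 83.0% at 12 vs 14. Reversal needs treated means near 12 mmol/L or more. The article gives no arm means, its 11.1 threshold is a diagnostic value rather than a 14-day mean on treatment, and it notes that fasting glucose is often normal in these patients.

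All of this stands, and it limits the weight of the point. It does not remove it: the article attaches non-inferiority to the listed outcomes and names no rule for reading the bands jointly.

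A reader might infer two stronger things. The first is that the trial could report less time above range overall for the worse arm. The documents do not support that, because time above range is reported at two levels and the upper one moves the right way. The second is that hypoglycaemia under NPH insulin could be hidden by the 3–3.9 band. That is not supported at usual means. Deeper lows are covered by the open <3 band, by event counts in total and by level, and by the severe-hypoglycaemia and safety outcomes.

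**Conclusion.** The point holds as a minor flaw in single secondary tests. Time in 10–13.9 mmol/L is not monotone in control, so a t-test or non-inferiority statement on it alone has no fixed meaning. With a true 2 mmol/L worsening, the test works at assumed means of 8 vs 10 and, with reduced power, at 9 vs 11. It is weak at 10 vs 12, nearly blind at 11 vs 13, and at 12 vs 14 favours the worse arm in about 26% of trials (90% with the smaller SDs). These figures rest on assumed arm means, on the assumed split of variance and on a normal model. The primary endpoint, mean CGM glucose, is untouched. The 3–3.9 band shares the structure, but reversal there is unlikely at usual means. The conclusion is confined to time shares and does not extend to the AUC or event-count outcomes.

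**What to change.** In TIR metrics, make the tested outcomes cumulative: time >10 and time >13.9 mmol/L without an upper cap, and time <3.9 and time <3 mmol/L, each as a percentage of recorded CGM time. Each then has one harmful direction. Keep 10–13.9 and 3–3.9 mmol/L as descriptive rows, with no separate between-group test or non-inferiority statement. Time in range stays as it is.

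The cost is a reworded endpoint list, which can be carried into the analysis plan that the article says will be agreed before the randomization code is added to the cleaned data. It needs the same CGM recordings and no extra patients. The downside is overlap: time >13.9 is part of time >10, and time <3 is part of time <3.9, so the results within each pair are correlated and should not be presented as independent findings.
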